### Participants

Patients with SD are recruited in the National Reference Center for Rare or Early Onset Dementias at the Pitié-Salpêtrière Hospital, at the Rothschild Ophthalmologic Foundation and at the Léopold Bellan Hospital in Paris. Patients are recruited based on the following inclusion criteria: (1) diagnosis of SD based on current research criteria [1] comprising progressive language impairment, single-word comprehension deficits and anomia, without sentence repetition impairment, agrammatism or motor speech disorders; (2) age > 18 years and (3) affiliation to a social security regime.

Non-inclusion criteria are the following: (1) psychiatric disorders or neurologic diseases other than SD; (2) contraindication for MRI, PET or tDCS such as presence of intracranial ferromagnetic devices, scalp or skull lesions or epilepsy; (3) MRI recordings revealing pathological processes other than those associated with SD; (4) severe aphasia (severity score < 3 in the Boston Diagnostic Aphasia Evaluation (BDAE) [47]); (5) Mini Mental State Examination (MMSE) [48] score < 15; (6) Frontal Assessment Battery (FAB) [49] score < 10; (7) Montgomery Asberg Depression Rating Scale [50] (MADRS) score ≥ 20, indicating a major depressive disorder; (8) not having the French language as a mother tongue; (9) being left-handed and (10) being under curatorship or tutorship. Prior to inclusion in the protocol all patients undergo a neuropsychological and speech therapist evaluation to check for inclusion/non-inclusion criteria, and to characterize global cognitive/language/semantic capacities on the basis of several published standard tests.

Healthy participants are recruited among hospital staff, caregivers and patients’ relatives via announcements in the neurology department. They are matched with the patients with SD on sex, age, handedness and number of years of education. Non-inclusion criteria for healthy participants are the following: (1) neurological or psychiatric disorders or physical deficits that can interfere with cognitive function; (2) contraindications to MRI or PET and (3) not having French language as mother tongue.

### Randomization

A computer-generated block randomization list has been prepared by the Clinical Research Unit of the Pitié-Salpêtrière - Charles Foix Hospital group. The randomization list is integrated into the electronic case report form (eCRF) and a randomization number assigning patients to one of the three stimulation conditions (anodal, cathodal or sham tDCS) is attributed automatically upon completion of inclusion/non-inclusion criteria. The randomization is not stratified by center of inclusion because all stimulation sessions and time-point evaluations are performed at the Pitié Salpêtrière Hospital.

### Stimulation administration

The stimulation procedure (electrode montage and stimulation parameters) is the same as the procedure used in our aforementioned pre-therapeutic study [45]. During the baseline visit patients undergo FDG-PET and MRI including anatomical 3D T1-weighted images. The T1-weighted images are registered in standardized Montreal Neurological Institute (MNI) space and the left and right ATL are identified and labeled with a 5-mm sphere centered on MNI coordinates (x = − 52, y = 2, z = − 28) and (x = 53, y = 4, z = − 32), respectively [51], using custom-made SPM8 (Statistical Parametric Mapping, Matlab Mathworks) procedure. Images are then denormalized in each patient’s native space. The day of the stimulation a scalp inspection is performed to verify the absence of skin lesions. Before the placement of the tDCS electrodes the scalp is carefully cleaned using an abrasive paste to limit impedance losses between the skin and the electrodes. Two round sponge electrodes, one acting as the active electrode (anodal or cathode) and the other as return (Sponstim®, 5.65 cm diameter, 25cm^2^ surface, NEuroelectrics, Barcelona, Spain) are placed under MRI guidance using a stereotactic neuronavigation system (Brainsight®, Rogue System®, Montreal, Canada). This procedure minimizes the distance between the labeled cortical target on a 3D reconstruction of each patient’s MR image and its closest (shortest Euclidian path) scalp location (Fig. 2).

**Fig. 2 Fig2:**
[figure not shown]
The three upper panels show, respectively, **a** coronal, **b** axial and **c** sagittal sections from magnetic resonance imaging (MRI) in a representative patient with semantic dementia (SD). The crosshair signals the location of the stimulation target in the left Anterior Temporal Lobe (ATL). **d** MRI-based frameless stereotactic navigation system device (Brainsight) employed for accurate targeting of the left ATL in SD patients. 3D brain curvilinear **e** cortical and **f** skin reconstructions from the MRI of a patient, provided by the neuronavigation system with a sphere indicating the left ATL target aimed by the stimulation

Stimulation is delivered using a wireless hybrid EEG/tDCS 8-channel neurostimulator (Starstim, NEuroelectrics, Barcelona, Spain). The active electrode is placed over the left ATL for left-anodal tDCS (between 10 and 20 EEG coordinates ~ FT7 and FT9), while the cathodal tDCS targets the right ATL (between ~ FT8 and FT10). In sham tDCS stimulation, the active electrode is placed over the same MNI coordinates as left-anodal tDCS. The return electrode is placed over the contralateral supra-orbital region with regards to the active electrode location (10–20 EEG coordinates AF8 for left anodal tDCS and AF7 for right cathodal tDCS). Additionally, six EEG scalp electrodes (NG Geltrode® Ag/AgCl, 1.0 cm^2^) provided by the same tDCS device, which allow for continuous monitoring of brain activity during the session, are placed in 10–20 EEG system locations F4, F3, C4, C3 and P4, P3.

During anodal or cathodal tDCS, current intensity is linearly increased over 30 s to reach a maximum of 1.59 mA. This level of tDCS intensity has been chosen to ensure similar levels of current density (0.06 mA/cm^2^) with our 25cm^2^ electrodes as those applied in previous post-stroke aphasia or PPA studies with larger leads [37, 45, 52]. Current is kept at this intensity for 20 min before being ramped down along 30 s at the end of the tDCS session. During sham stimulation the tDCS current is ramped up and down along 30 s at the initial and final phase of the session but is turned off during the 20 min session. This process makes active (anodal or cathodal) and sham stimulations similar (same somatosensory skin sensations) as required by a double-blind design. During each stimulation session, values of mean voltage (V), mean current intensity (uA) and mean impedance (Ohm), directly provided by the stimulation software, are recorded for means of tDCS verification intents. Treatment duration has been chosen based on previous studies showing beneficial tDCS effects with the same amount of time (e.g., [44, 45]). During tDCS sessions patients perform a language-neutral visuo-motor task on a laptop screen consisting of pressing the space bar on a computer keyboard every time a slowly moving dot contacts the edge of a surrounding rectangle. This task is intended to limit variability in neural activity states across sessions and patients (forcing patients to maintain vigilance) without interfering with language processes and tasks. At each session, performances (number of trials, number of successes and number of errors) in the visuo-motor task are recorded.

To ensure safety and comfort and to assess the tolerance of patients to stimulation, immediately after each tDCS session patients are asked to complete a tDCS adverse effects questionnaire [53] that measures, through a rating scale, patients’ sensations in a set of the most frequent adverse effects reported in tDCS studies such as itching, tingling, burning sensations, skin redness or sleepiness.

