**Fig. 1 Fig1:**
[figure not shown]
**a** Flow diagram from patients’ selection to the end of their participation in the study. tDCS, transcranial direct current stimulation; MRI, magnetic resonance imaging; PET, positron emission tomography; EEG, electroencephalography. **b** Standard protocol items: recommendations for Interventional Trials (Additional file 1). Table defining the different evaluations or interventions (left column) that would be performed for each study period or time point (top rows)

Language/semantic assessments are applied at the four time points by a set of computer-based tasks. For each task, we have developed two equivalent versions matched on various linguistic variables, which are used alternatively either at baseline or during follow-up evaluations, in a counterbalanced order across patient subgroups to avoid test/re-test confounds. Neuroimaging acquisitions (structural MRI, resting-state fMRI, FDG-PET) are performed at baseline and the 2-week time point. We also acquire resting-state electroencephalogram (EEG) recordings at baseline and after the end of tDCS sessions (3-day time point) given that patients with SD might have an altered pattern of resting state neuronal synchronizations [46].

To ensure double-blinding a first investigator (stimulator) performs and supervises the tDCS sessions, whereas a second investigator (evaluator) conducts the langue/semantic tasks, blinded to the stimulation condition (anodal, cathodal or sham). During sham stimulation, tDCS current is ramped up and down along 30 s respectively during the initial and final phases of the session, to emulate the transient skin-itching sensations characterizing active anodal or cathodal stimulation. Unnoticed by the patients, the stimulation unit is turned off during the 20-min sham tDCS session.

Stimulation sessions are applied daily for 10 days (Monday to Friday for 2 weeks). Each tDCS session lasts for 20 min. The direct current has an intensity of 1.59 mA (25cm^2^-round electrodes, current density of 0.06 mA/cm^2^). A group of 20 healthy subjects are also evaluated at baseline to provide normative values for language/semantic tasks and for imaging measures. Healthy participants do not undergo tDCS treatment and are only assessed once with the same language/semantic tasks and neuroimaging assessments performed by SD patients.

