The primary endpoint of the *STIM-SD* protocol is to evaluate the potential therapeutic efficacy of multiday tDCS (10 days) on language/semantic performance in patients with SD (see the section “Language/semantic tasks” – the semantic association task). In addition, we will also (1) assess the time course of potential language/semantic improvement through the application of four follow-up time points; (2) assess neuroimaging biomarkers (PET and MRI) that could reflect stimulation-induced neuroplasticity and response to stimulation; (3) compare the effects of left-anodal and right-cathodal tDCS to define the most efficient stimulation modality; (4) identify biomarkers that could individually predict tDCS impact and (5) improve the understanding of the semantic roles of the left and right ATL and their potential structural connectivity, contributing to the definition of anatomic-functional models of semantics.

The protocol has been approved by the local Ethics Committee and is registered in ClinicalTrials.gov with the identifier NCT03481933 and the study title “‘Evaluation of a Transcranial Stimulation with Direct Current on Language Disorders in Semantic Dementia (STIM-SD)”*.* Written informed consent is obtained from all patients and healthy subjects before the onset of any of the study procedures. All research protocol visits take place at the same site, the Pitié-Salpêtrière Hospital. Two additional centers contribute to the protocol by recruiting patients with SD.

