### Computational models of tDCS current magnitude and distribution

There is evidence that the thickness of the skull, the volume of the cerebrospinal fluid in the subdural space and the distance from the targeted region in the brain to the tDCS anode or cathode account for up to 50% of the spatial variation of the electric field strength [61–63]. Kim et al. [64] found that performance improvement in a working memory task correlated with the simulated current magnitude, suggesting that inconsistent behavioral outcomes of tDCS might be partly due to individual anatomical differences.

A computational approach of modeling should allow for defining if and how tDCS current magnitude and distribution in the heads of individuals can differ and how these differences will affect clinical outcomes. Individual computational models will be produced using the open-source tool ROAST [65] to simulate tDCS current magnitude and distribution using the anatomical 3D T1-weighted MRI images of each patient (Fig. 5). Then, correlation will be tested between model-estimated data for current magnitude values and clinical data, specifically the changes in scores in the SA task from baseline to post-stimulation. A region of interest (ROI) will be defined and the mean of the 5% highest electric field values in this region will be obtained for each patient. More specifically, we will define the left anterior/middle temporal lobe as our ROI, because this region is primarily damaged in SD and it is the region targeted during the stimulation. Finally, measures of thickness of the different tissue layers (skin, skull, cerebrospinal fluid volume, gray matter and white matter) and distances between the stimulation target (ATL) and the stimulating electrode will be obtained and regression models will be computed to identify specific features that most influence changes in current magnitudes. This will allow us to identify the characteristics that might influence patients’ responses to tDCS and help predict if an individual patient might benefit from tDCS treatment.

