To identify imaging bio-markers of stimulation-induced neuroplasticity, we will analyze cortical metabolism and resting-state functional connectivity. PET images will be used for cortical metabolism, to analyze tissue metabolic activity and regional glucose uptake in the brain. A voxel-based analysis, using the Statistical Parametric Mapping (SPM) software [66], will be implemented to highlight regional differences in metabolism between the images obtained at baseline and post-stimulation. The resting-state fMRI sequence will be explored to study the status of functional connectivity within the language/semantic networks and possible alterations within it between baseline and post-stimulation images. Quantification of functional connectivity will be based on integration measures in specific networks established from the known anatomy, on indices derived from the graph theory or information theory. Cortical regions of interest will be obtained automatically using SPM toolboxes. More specifically, the language/semantic network will include the middle and anterior portions of the lateral ATL, the inferior frontal gyrus, the dorsomedial and ventromedial prefrontal cortex and the inferior parietal lobe. To study the neurophysiological impact of tDCS on specific brain networks, resting-state EEG datasets obtained at baseline and 3 days after the end of the 10 tDCS sessions will be also analyzed. Data will be filtered (4–40 Hz) and power distribution and local synchrony calculated across frequency bands and compared. Functional connectivity maps across the electrodes will be estimated by calculating the phase-lockimg value between the eight EEG leads and have them compared across in pairs.

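### Active and return electrodes are tied together in both active arms, so arm contrasts show the effect of a montage and not of one ATL; the current-model region is also off target in the right-cathodal arm

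*Protocol article*

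**What the plan says.** Stimulation administration describes one electrode type for both positions: "Two round sponge electrodes, one acting as the active electrode (anodal or cathode) and the other as return (Sponstim®, 5.65 cm diameter", with a surface of 25 cm2. During active tDCS, "current intensity is linearly increased over 30 s to reach a maximum of 1.59 mA". Study design gives the density: "The direct current has an intensity of 1.59 mA (25cm^2^-round electrodes, current density of 0.06 mA/cm^2".

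On placement, "The return electrode is placed over the contralateral supra-orbital region with regards to the active electrode location": AF8 for left-anodal and AF7 for right-cathodal. The legend of Fig. 5 labels the AF8 electrode of the left-anodal montage as the cathode. Sham uses the left-anodal ATL position.

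The Introduction says that tDCS polarises a wide stretch of cortex between the two electrodes, that anodal stimulation excites and that cathodal stimulation inhibits. Data analyses counts among the language/semantic network "the inferior frontal gyrus, the dorsomedial and ventromedial prefrontal cortex and the inferior parietal lobe".

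Among the further objectives in Study design, the third compares the two modalities to find the more efficient one. The fifth is to "improve the understanding of the semantic roles of the left and right ATL".

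For the individual current models, "A region of interest (ROI) will be defined and the mean of the 5% highest electric field values in this region will be obtained". That region is the left anterior/middle temporal lobe, chosen because it is the most damaged and because it is said to be the one stimulated. The modelled values are to be correlated with change in SA score.

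**The concern.** The right-cathodal arm is motivated by release of the left language network from right-hemisphere inhibition, and the left-anodal arm by excitation of the left ATL. Each arm also places an electrode of opposite polarity over the other side of the forehead, near prefrontal cortex. By the article's own account an anode over the left supra-orbital region could excite tissue there, and prefrontal regions belong to the network under study. A gain in the right-cathodal arm could therefore be reported as release from right-ATL inhibition when a left prefrontal contribution has not been excluded. The same holds in mirror image for the left-anodal arm.

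The current models are the natural place to examine this, but they read the field from one region only, and in one of the two active arms that region is not the target. What is at stake is the mechanistic reading and the dose-response analysis, not the primary test.

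**Working it through.** **1. Reproduce the stated density.** Inputs: 1.59 mA, 25 cm2, diameter 5.65 cm (Stimulation administration).
- Density = current / area = 1.59 / 25 = 0.0636 mA/cm2.
- Area from the diameter = π × (5.65 / 2)² = 25.07 cm2, giving 1.59 / 25.07 = 0.0634 mA/cm2.
- Both round to the printed 0.06 mA/cm2.

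**2. Density at the return electrode.** In a two-electrode circuit the same current crosses both electrodes. With equal areas the return density is also 0.0636 mA/cm2, with opposite sign. The ratio to the active electrode is 1.0.

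**3. Lay out the arms.**

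| Arm | n | Active electrode | Return electrode |
|---|---|---|---|
| Left-anodal | 20 | anode, left ATL | cathode, right AF8 |
| Right-cathodal | 20 | cathode, right ATL | anode, left AF7 |
| Sham | 20 | left-ATL position, current off during the 20 min | not stated separately |

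The AF8 polarity is printed in the Fig. 5 legend. The AF7 polarity follows from the circuit, since the active electrode in that arm is the cathode. Both active arms have the anode on the left and the cathode on the right. Target and return site are completely tied within each arm, because no arm has the same target with a different return site. Contrasts with sham, or between the active arms, therefore estimate effects of complete montages.

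**4. Compare the modelled region with the targets.**

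| Arm | Stated target | Region read from the model | Match |
|---|---|---|---|
| Left-anodal (20) | left ATL | left anterior/middle temporal lobe | yes |
| Right-cathodal (20) | right ATL | left anterior/middle temporal lobe | no |

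The reason given for the region, that it is the one stimulated, does not hold for 20 / 40 = 50% of the active patients. In that arm the only electrode on the left is the return anode at AF7. The article names no field value to be taken from the right ATL or from prefrontal cortex.

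**5. What a field-response correlation can show with 20 patients.** By Fisher's z, two-sided 5%, 80% power: z = (1.96 + 0.84) / √(20 − 3) = 2.80 / 4.12 = 0.68, so r = tanh(0.68) ≈ 0.59. Only a strong association within an arm is likely to be detected. Fields at several regions come from the same head model and current, so they are probably correlated with one another and hard to separate.

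**The case against.** The strongest reply is that the trial does not need to locate the effect. The third objective compares the modalities as delivered, and randomisation answers that. The comparison with sham, the endpoint, the error rate and the sample size are untouched. All of this stands. A reader might infer that the montage undermines the choice between the two modalities, but the article does not support that.

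The fifth objective is exploratory, and the analysis that Data analyses ties to it is diffusion imaging of the connections between the two ATLs, which the return electrode does not confound at baseline. This also stands, so it would be too strong to say that the objective cannot be pursued. Diffusion imaging describes connections, however. It does not show where a stimulation effect arose.

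A reader might also say that the plan discards the only measure able to separate the explanations. It does not. Voxel-based PET, resting-state fMRI in a network that includes frontal regions, EEG and the executive task (EXE) all bear on the question indirectly. They are limited: the PET and fMRI are taken 2 weeks after stimulation and may show downstream change, and EXE tests executive function, not a prefrontal semantic effect. EXE would still correctly flag a non-semantic effect, so it is a partial safeguard and not a further fault.

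Finally, equal density at the scalp does not mean equal effect in the cortex. The article itself says that skull, cerebrospinal fluid and distance account for up to half of the spatial variation in field strength. It gives no cortical field at the return site and does not place the listed network regions beneath AF7 or AF8. A prefrontal contribution is therefore plausible on the article's own account, but not shown.

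None of these replies answers the mismatch between the modelled region and the right-cathodal target.

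**Conclusion.** The point holds in a limited form. In all 40 active patients the return electrode matches the active one in area and current, with opposite polarity, and no arm varies its site. Contrasts between arms alone cannot attribute an effect to the left or right ATL. This limits statements about the semantic role of each ATL and about release from inter-hemispheric inhibition. It does not touch the efficacy claim or the choice between modalities.

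Separately, the stated reason for the modelled region is wrong for the right-cathodal arm, and the planned field-response correlation would not use the field at the target in 20 of the 40 active patients.

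The conclusion rests on two assumptions: that both sponges have the stated 25 cm2 area, as the single description implies, and that the AF7 electrode is the anode in the right-cathodal arm, as the circuit requires. It does not assume that the cortical effect at the return site equals that at the target. How far the left temporal field in the right-cathodal arm reflects the return electrode cannot be judged from the article.

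**What to change.** Leave the stimulation unchanged.

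- In the section on computational models, define the target region by arm: left ATL for left-anodal, right ATL for right-cathodal. Correct the stated reason for the region accordingly.
- From the ROAST models already planned for each patient, also extract the field in the prefrontal cortex on the return-electrode side and in the inferior frontal gyrus.
- Report the association of each field with SA change by arm, labelled exploratory, and state the likely collinearity and the 20 patients per arm. Do not let a rule that one field carries the association and another does not decide a conclusion; the sample is too small for that.
- Attribute treatment effects to the montage. Describe statements about the semantic role of either ATL, or about release from inter-hemispheric inhibition, as supported and not established by these analyses. The third objective needs no change.

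The cost is a few more regions read from existing models, some extra exploratory analysis and a more modest mechanistic claim. No new data, visits or patients are needed.
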